#### Daily measures

As mentioned earlier, the daily assessment of emotions could improve self-awareness about the emotional status and thus contribute to better emotional regulation. To control for this, the two mobile applications (EMI app and EMA app) will assess the same variables daily. These will include joy, fatigue, sadness, anxiety, anger, burnout, sleep quantity, sleep quality, perceived stress, and implemented ER (coping) skills, which have been found to be relevant emotional states reported by healthcare workers [10, 11]. Each variable will be responded using an 11-point slider question (from 0 to 10). Table 1 contains a description of the items used in the study. Items from 1 to 5 have been previously validated in a previous study [58], while items 6 to 10 have been elaborated ad hoc for this investigation. All items use the same format, except item 7 (sleep quantity), where the user has to select the number of hours slept. The users will receive a daily reminder to answer the 10 questions. The purpose of this reminder is to facilitate adherence. However, following the real-time and real-world philosophy of ecological and momentary assessments, the users will be able to open the app and answer to these questions on demand at any moment.

**Table 1 Tab1:** Daily assessment

Item	Construct assessed	Description
1^a^	Joy	Please, indicate the intensity of your CURRENT HAPPINESS 0 = No happiness-------------------------------10 = Extremely happy
2^b^	Fatigue	Please, indicate the intensity of your CURRENT FATIGUE 0 = No fatigue--------------------------------10 = Extreme fatigue
3^a^	Sadness	Please, indicate the intensity of your CURRENT SADNESS 0 = No sadness-------------------------------10 = Extreme sadness
4^a^	Anxiety	Please, indicate the intensity of your CURRENT ANXIETY 0 = No anxiety-----------------------------10 = Extremely anxious
5^a^	Anger,	Please, indicate the intensity of your CURRENT ANGER 0 = No anger-------------------------------10 = Extremely angry
6^b^	Burnout	Please, indicate your degree of agreement with the next statement: “I am burned out from my work” 0 = totally disagree----------------------------------------10 = totally agree
7^c^	Sleep quantity	How many hours have you slept in the last 24 h?
8^c^	Sleep quality	Has WORK interfered with the quality of your SLEEP tonight? 0 = No Interference----------------------10 = Maximum Interference
9^c^	Perceived stress	Please, indicate the intensity of your CURRENT STRESS 0 = No stress------------------------------10 = Extremely stressed
10^c^	Self-perception of coping skills	To what extent do you feel CAPABLE OF COPING with your problems right now? 0 = No capable---------------------------------10 = Extremely capable

Note: ^a^Items extracted from Suso-Ribera et al. [58]. ^b^Item inspired by Morgantini et al. [17]; ^c^Items elaborated ad hoc for the current study

### Interventions

Two active conditions will be used in this study, that is, (1) the EMI intervention and (2) the EMA condition. Because, Android OS represents 80% of the users in Spain [89], the apps for this study have been developed only in this operating system. Further development in other mobile operative systems will be done after the results have been analyzed.

#### Monitor emocional APP (EMA condition)

“MONITOR EMOCIONAL” is an app for ecological momentary assessment developed in Android OS (https://play.google.com/store/apps/details?id=monitoremocional.code&gl=ES). To use this app, users will have to obtain a code from the researcher. The app will be active during 2 months. When the users open the app, the 10 daily items from Table 1 will be showed in a linear manner. After the two-month daily evaluation, the app will suggest the users to uninstall the application and will stop sending them the reminders to complete the evaluations. The users will be able to use the app any moment during the two-month period. The intervention aspect of this app is grounded on the first step of the emotion regulation process, that is, self-awareness of emotions through daily assessment.

#### CUIDA-TE APP (EMI condition)

“CUIDA-TE” (which could be translated to “TAKE CARE OF YOURSELF”) is an app for EMI developed in Android. As in the previous app, to use the CUIDA-TE app the user will have to obtain a code from the researcher. The app will be active during 2 months. Again, when users open the app the 10 daily items from Table 1 will be showed in a linear manner. The interventions are mediated by the intensity and type of emotional state. Thus, when the user reaches the specific scores detailed in Table 2, an EMI will be activated to offer the intervention objects linked with this score and construct. The clinical alarms in Table 2 were set after a series of meetings with experts in clinical psychology and mood disorders. For the cut-offs of severe, moderate, and mild levels of symptomatology, we followed the recommendations from past research (0–4 for mild, 5–6 for moderate, and 7–10 for severe) [90]. Considering the results on ER strategy choice research [49, 53], when participants report a low-moderate emotional intensity, interventions related to cognitive reappraisal and behavioral change will be proposed. On the contrary, when participants indicate high emotional intensity, strategies focused on attentional deployment such as relaxation, mindfulness, and distraction will be indicated.

**Table 2 Tab2:** Structure of the ecological momentary intervention

Item	Construct assessed	Activate EMI when item scores	Ecological momentary intervention (EMI)
1	Joy	*High:* from 7 to 10	Savoring
2	Fatigue	*High:* from 7 to 10	Psychoeducation in self-care Mindfulness 5 senses Relaxation-Paced breathing exercise
3	Sadness	*High:* from 7 to 10	Mindfulness in a joyful environment Reminiscence
		*Moderate:* from 5 to 6 during 2 consecutive days.	Psychoeducation of emotion’s function Checking the facts Behavioral activation (based on goals and values)
4	Anxiety	*High:* 7 to 10	Safe place exercise Relaxation-Paced breathing exercise Mindfulness in a relaxing environment
		*Moderate:* 5–6.	Cope ahead of time
5	Anger	*High:* 7–10	STOP exercise Mindfulness in a relaxing environment Relaxation-Paced breathing exercise Relaxation-Progressive Muscle relaxation exercise Safe place exercise
		*Moderate:* 5–6	Problem solving Acceptance with the body
6	Burnout	*High:* 7–10	Psychoeducation on self-care Mindfulness 5 senses Mindfulness in a relaxing environment
		*Moderate:* 5–6 during 3 consecutive days.	Behavioral activation (based on goals and values).
7	Sleep quantity	*Low:* 0–4 h during 2 consecutive days.	Psychoeducation: The need of self-care to be able to care others.
		*Moderate:* 5–6 h during 4 consecutive days	Psychoeducation on sleep habits Psychoeducation on self-care
8	Sleep quality	*High:* 7 to 10	Savoring
		*Moderate:* 5–6 during 2 consecutive days	Psychoeducation on sleep habits Mindfulness in a relaxing environment
9	Perceived stress	*HIgh:* 7 to 10	Safe place exercise Mindfulness in a relaxing environment Relaxation-Paced breathing exercise
		*Moderate:* 5–6 during 5 consecutive days.	Psychoeducation: The need of self-care to be able to care others. Behavioral activation (based on goals and values) Problem solving
10	Self-perception of coping skills	*Low:* from 0 to 3.	Cope ahead of time
		*Moderate: 5* or over during 2 consecutive days.	Problem solving Behavioral activation (based on goals and values)

The interventions detailed in Table 2 consist of treatment strategies and exercises based on principles of different evidence-based transdiagnostic cognitive behavioral interventions that aim to regulate the problematic emotion experienced. Most of the strategies were adapted and abbreviated from the UP [91] and DBT treatments to be delivered through a smartphone as an EMI (using multimedia objects). In the following lines we briefly describe the intervention developed for each emotion. As a note, psychoeducation components were included in several EMIs to introduce the background of the intervention.

##### 1.-joy

When joy is reported to be high, the goal would be to include interventions to up-regulate positive emotion (i.e., increase its intensity or duration), which has been associated with fewer symptoms of psychopathology and increased reports of life satisfaction and well-being [92]. Different exercises are proposed to practice focusing on positive such as *savoring* (i.e., focus our attention on what is positive in our day-to-day life).

##### 2.-fatigue

Fatigue usually refers to an impairment in task performance at an individual’s normal capacity. The major cause of fatigue for healthcare workers are disruptions of sleep and other health habits [93], which have been aggravated after the COVID-19 pandemic [9]. Therefore, when fatigue is high, participants will be first directed to read a psychoeducation self-care module to improve health habits. After that, other mindfulness (*observe with five senses*) and relaxation (*paced-breathing*) exercises from DBT will be delivered to increase awareness and a sense of calm, respectively [24].

##### 3.-sadness

Mindfulness and positive reminiscence interventions are proposed when sadness is high. Mindfulness practice has been associated with increases in happiness [94] and decreases in depression [95]. An example of a mindfulness exercise is to *observe a joyful environment* of a virtual nature scenery. Remembering positive personal past memories is another recommended exercise. However, when sadness is moderate, reappraisal, which leads to a decrease in negative emotion experience and expression [96], and behavioral activation are recommended. An example of a reappraisal exercise is *checking the facts*, a skill from DBT [24]. Exercises of *behavioral activation* to achieve personal goals and values are also recommended to decrease depression [24].

##### 4.-anxiety

Different exercises of distraction (*safe place exercise*), relaxation (*paced breathing exercise),* and mindfulness (*observing nature with relaxing instructions*) are proposed for high anxiety scores. The ultimate goal of these techniques in the context of this intervention is to induce relaxation and calm as ways to rapidly reduce emotional arousal [24]. For moderate anxiety scores, a cognitive change technique named *cope ahead* is proposed to develop effective strategies to manage anxiety ahead of time using imagination [24].

##### 5.-anger

When anger is high, distraction (*STOP exercise*), mindfulnes*s* (in a relaxing virtual nature), and relaxation (*paced breathing and progressive muscle relaxation*) exercises are proposed. An example of EMI for high anger is the *STOP skill* that instructs participants to step back, observe, and proceed mindfully towards the situation that sets up the emotion [24]. For moderate anger scores, *problem solving* is aimed to change difficult situations when an emotion fits with the facts [24], whereas acceptance refers to accepting the situation or incapacity to deal with it [97]. This last strategy is especially useful in situations that cannot be easily modified or reappraised (e.g., deaths that resulted from COVID-19) and has been found to be protective at both psychological and physical levels [97]. Examples of acceptance interventions are short exercises to practice *acceptance with the body* [24].

##### 6.-burnout

Research has shown that the COVID-19 pandemic has negatively impacted the feeling of burnout in healthcare professionals [9]. When burnout is high, as recommended with fatigue, participants will be first directed to a psychoeducational module. After that, mindfulness exercises to increase emotional awareness and a sense of calm will be proposed. On the contrary, when burnout is moderate, working on goals and values through behavioral activation exercises is recommended.

##### 7,8.-sleep quantity and quality

Disruption of the circadian sleep rhythm and sleep deprivation are common in healthcare professionals [93]. Both sleep quantity and quality will be measured. When sleep quantity is low or moderate (assessed as the number of sleep hours), psychoeducation on sleep and self-care habits are recommended. Regarding sleep quality, when this is high, participants will be instructed to practice *savoring* of the moment to increase awareness about the positive experience. On the contrary, when this is moderate, the participants will receive mindfulness and relaxation exercises to increase awareness and calmness.

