**Methods:**

In this three-arm, randomized controlled trial (RCT) the study sample will be composed of a minimum of 174 healthcare workers. They will be randomly assigned to a 2-month EMI group (CUIDA-TE APP, *n* ≥ 58), a 2-month ecological momentary assessment (EMA) only group (MONITOR EMOCIONAL APP, n ≥ 58), or a wait-list control group (no daily monitoring nor intervention, n ≥ 58). CUIDA-TE will provide EMI if EMA reveals emotional problems, poor sleep quality/quantity, burnout, stress, or low perceived self-efficacy when regulating emotions. Depression will be the primary outcome. Secondary outcomes will include emotion regulation, quality of life, and resilience. Treatment acceptance and usability will also be measured. Primary and secondary outcomes will be obtained at pre- and post-intervention measurements, and at the 3-month follow-up for all groups.

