##### 10.-Self-perception of coping skills

Research has revealed that positive coping strategies have a beneficial impact on mental health outcomes [100]. When self-perception of coping skills is low, practicing *cope ahead* can help healthcare professionals to develop and observe themselves practicing effective coping skills on the imagination in order to later put them into practice in real stressful situations. On the other hand, for moderate scores, problem solving and behavioral activation are recommended to develop solutions and take steps to achieve personal values respectively.

Whenever a user scores within the parameters defined in Table 2, an EMI will be activated and the interventions will be presented in the form of exercises in multimedia and self-applied format (audio, video, text, or little webpages). The exercises will be stored in the library section, so that the user will be able to revise the content at will. An example of the flow followed by the users using the EMI app is shown in Fig. 2.

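### Item 8's trigger runs against its own scale, so the worst work interference with sleep prompts only savoring; item 10's moderate coping trigger has no upper limit

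*Protocol article*

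**What the plan says.** **The item.** Table 1 (Daily measures) words item 8 as "Has WORK interfered with the quality of your SLEEP tonight" and sets its upper end at "10 = Maximum Interference". A higher score means worse sleep.

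**The trigger.** Table 2 (CUIDA-TE APP section) has two rows for item 8. Scores of 7 to 10 lead to savoring and nothing else. Scores of 5 to 6 on two consecutive days lead to "Psychoeducation on sleep habits Mindfulness in a relaxing environment".

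**The rationale.** The section on sleep quantity and quality says: "Regarding sleep quality, when this is high, participants will be instructed to practice" savoring, so that the user becomes more aware of a positive experience. The section on joy places savoring among "interventions to up-regulate positive emotion", used when joy is high.

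**The status of the table.** The section on coping skills makes Table 2 the operating rule: "Whenever a user scores within the parameters defined in Table 2, an EMI will be activated".

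**Item 10.** Perceived coping ability is scored from 0 up to "10 = Extremely capable". Table 2 labels 0 to 3 as low, and labels 5 or more on two consecutive days as moderate. The accompanying text reserves problem solving and behavioral activation for moderate scores.

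**The concern.** The item, the trigger table and the explanatory text disagree on which end of item 8 is bad. Choosing savoring deliberately for poor sleep could have been defended, but the stated reason rules that out, since the exercise is offered because sleep is assumed to be good. Followed literally, the table gives people with the greatest work-related sleep disturbance an exercise for prolonging a good feeling, while people with less disturbance get the sleep content.

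This matters for the comparison the trial is built on. Both apps ask the same ten daily questions, so what separates EMI from EMA is the content matched to the reported state. If the app is coded as published, two of the ten items deliver partly mismatched content, and the EMI arm is not quite the intervention it is described as. The article says the apps have already been developed, so the published rule may already be in the code.

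**Working it through.** No published figure needs reproducing here. The check lists every score from 0 to 10 against the Table 1 anchors, the Table 2 triggers and the severity bands in the CUIDA-TE APP section (0–4 mild, 5–6 moderate, 7–10 severe).

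**Item 8 as published** (x = interference, 10 = worst)

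| Score x | Number of scores | Content from item 8 |
|---|---|---|
| 7–10 | 4 of 11 | savoring only |
| 5–6, two consecutive days | 2 of 11 | sleep-habit psychoeducation, mindfulness |
| 0–4 | 5 of 11 | none |

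**Item 8 if the app silently reverses the score** (r = 10 − x; the document does not state this)

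| Reversed score r | Interference x | Number of scores | Content from item 8 |
|---|---|---|---|
| 7–10 | 0–3 | 4 of 11 | savoring only |
| 5–6, two consecutive days | 4–5 | 2 of 11 | sleep-habit psychoeducation, mindfulness |
| 0–4 | 6–10 | 5 of 11 | none |

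Neither reading works. As published, the worst sleep gets the wrong content. Reversed, it gets no item 8 content at all, because Table 2 has no row for poor sleep quality.

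**Comparison with similar items.** Six other items are scored so that higher is worse: fatigue, sadness, anxiety, anger, burnout and stress (2, 3, 4, 5, 6 and 9). All six include a mindfulness exercise at 7 to 10. This follows the stated principle that high intensity calls for relaxation, mindfulness or distraction. Item 8 is the only higher-is-worse item that departs from it.

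**Other routes to sleep-habit content.** In Table 2 the sleep-habit module appears in two rows only: item 7 at 5–6 hours for four consecutive days, and item 8 at 5–6 for two consecutive days. By the table, a user with lasting interference of 7 to 10 who sleeps seven or more hours, or four or fewer, is never directed to it. The text on low sleep quantity is looser than the table here and also mentions sleep habits.

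**Item 10 as published** (10 = best)

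| Score | Number of scores | Trigger |
|---|---|---|
| 0–3 | 4 of 11 | low |
| 4 | 1 of 11 | none |
| 5–10, two consecutive days | 6 of 11 | moderate |

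The protocol's own moderate band is 5–6. Capping the trigger there would leave 2 of 11 scores. A cap at 4–6, which also closes the gap at 4, would leave 3 of 11.

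**The case against.** **The app may not follow the table.** Three printed places disagree, and the document does not show which one the code uses. The slip could lie in the item's wording, in Table 2 or only in the write-up. This stands as a limit: the inconsistency is certain, but its effect on users is conditional on the code. It does not remove the fault, because the plan itself makes Table 2 the activation rule.

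**Other items supply suitable content.** High fatigue, anxiety, burnout and stress all trigger mindfulness, short sleep triggers psychoeducation, and exercises stay in a library. This limits the overall effect. It does not help a user whose only complaint is poor sleep quality.

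**The abstract is not contradicted.** It says "CUIDA-TE will provide EMI if EMA reveals emotional problems, poor sleep quality/quantity", and some EMI does fire at 7 to 10. On the published reading that is correct: the mismatch is in the content. On the reversed reading, interference of 6 to 10 would trigger nothing from item 8, which would conflict with the abstract.

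**The counts are points on a slider.** They are not participants or days. This stands; they describe the rule and say nothing about how often it misfires.

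**Item 10 is minor.** Offering problem solving to people who already feel capable is not shown to be harmful, and untriggered scores are common in Table 2. Both points are fair. The label still does not fit its range, and the score of 4 differs from the usual untriggered range because it lies between two triggering bands. It is a side point.

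**Conclusion.** The concern holds. Item 8's high trigger runs against the item's own scale: 4 of 11 scores, the worst ones, lead only to an exercise intended for a positive state, and simple reversal would leave 5 of 11 scores (interference 6 to 10) without item 8 content. Item 10's moderate trigger covers 6 of 11 scores, including the top of the scale, and this is the lesser fault.

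The conclusion rests on the tables as printed and on the absence of any statement of reverse coding. Whether users would receive the wrong content depends on app code that is not shown. The dilution of the EMI versus EMA contrast cannot be sized, because score frequencies are not given and other items fire alongside. Randomization, the primary outcome, sample size and error rates are not affected.

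**What to change.** Before recruitment starts:

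1. **Table 2, item 8.** Assign sleep-habit psychoeducation and mindfulness or relaxation content to interference of 7 to 10 as well as to 5–6. Move savoring to low interference (for example 0–4, the mild band) or drop it. If the team prefers to reword the item so that 10 means best sleep, a new row for poor sleep quality must be added; reversal alone is not enough. The choice of exercises is for the clinical team.
2. **Sleep paragraph.** Describe the triggers in terms of interference, so that *high* has one meaning throughout.
3. **Table 2, item 10.** Cap the moderate trigger, for example at 5–6 on two consecutive days, and decide deliberately whether a score of 4 belongs to low, to moderate or to neither.
4. **App.** Check the trigger code for both items against the corrected table and change it where it differs.

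The cost is two table rows, one paragraph and a check of two trigger rules. Sample size and assessments stay as they are.

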##### 9.-perceived stress

This refers to the degree to which people evaluate life situations as stressful [98]. Research has shown that perceived stress has increased among health care professionals working during the COVID-19 [99]. In the study, when perception of stress is high, the same exercises proposed for anxiety will be recommended. As opposed to this, when stress levels are moderate, strategies to achieve behavioral change such as problem solving and behavioral activation will be proposed. In addition, a psychoeducational self-care module will also be presented for moderate stress.

##### 10.-Self-perception of coping skills

Research has revealed that positive coping strategies have a beneficial impact on mental health outcomes [100]. When self-perception of coping skills is low, practicing *cope ahead* can help healthcare professionals to develop and observe themselves practicing effective coping skills on the imagination in order to later put them into practice in real stressful situations. On the other hand, for moderate scores, problem solving and behavioral activation are recommended to develop solutions and take steps to achieve personal values respectively.

Whenever a user scores within the parameters defined in Table 2, an EMI will be activated and the interventions will be presented in the form of exercises in multimedia and self-applied format (audio, video, text, or little webpages). The exercises will be stored in the library section, so that the user will be able to revise the content at will. An example of the flow followed by the users using the EMI app is shown in Fig. 2.

